### Randomisation and concealment

Participants will be randomised in a 1:1 ratio to either intervention or control. Allocation will be assigned using a minimisation algorithm balancing on recruiting site, CYP age (5–10, 11–15, 16–17 years) and sex, incorporating a probabilistic element to allocation. The allocation algorithm was created by Nottingham Clinical Trials Unit (NCTU) in accordance with their standard operating procedure. Allocation is concealed using an automated web system operated by NCTU.

Randomisation is automatically generated within the online system following submission, and automated verification, of baseline data by the primary participant. Participants are presented with their allocation and further instructions on-screen with email confirmation. Instructions for DAWBA completion are included for those in the intervention arm. Email confirmation is sent to the coordinating centre and site research team.

It will not be possible to blind participants, site researchers, clinicians and some trial staff to treatment allocation, but treatment allocation data will be restricted to those trial staff who require access to facilitate trial conduct. In particular, it will not be fully possible to blind researchers conducting data collection from records. However, any possible diagnoses identified from the CAMHS records will be recorded verbatim on the data capture form and will be subject to adjudication by the trial adjudication committee (members of the trial management group (TMG)). The committee will be blinded to treatment allocation and participant ID.

The risk of contamination between arms is considered low. Access to the DAWBA, and provision of the DAWBA report, is only provided to participants in the intervention arm. SDA tools are not current practice in standard care and it is unlikely that control participants will be asked to complete these at the point of referral receipt. DAWBA completion occurring outside the trial for control arm participants will be collected during follow-up.

### Interventions

#### Development and Well-Being Assessment

The trial intervention is the DAWBA.^24^ The DAWBA has a modular structure, with only those modules relevant to emotional and comorbid disorders included; separation anxiety, specific phobia, social phobia, panic and agoraphobia, generalised anxiety, post-traumatic stress disorder, obsessive–compulsive disorder, depression, oppositional defiant disorder and conduct disorder. Whereas, the strengths and difficulties questionnaire, bipolar disorder and body dysmorphic disorder are not included in the STADIA-specific DAWBA report as these modules do not generate diagnostic predictions. No free-text responses are collected.

The DAWBA will be self-reported by participants via the secure, standalone online platform created and maintained by the DAWBA developer.^24^ Access is by a unique ID number and password, assigned at the point of randomisation via a stock control system integrated into the randomisation system, ensuring accountability of DAWBA slot allocation.

The DAWBA may be completed by the parent/carer and/or CYP aged 11+, depending on the consent and participation arrangements (table 1) DAWBA completion will be monitored and the STADIA researcher will support and encourage completion. Participants will be able to complete the DAWBA in a telephone call with the STADIA researcher if required. Participants are asked to complete all modules of the DAWBA presented to them. Should the DAWBA be only partially completed by respondents the report will be based only on fully answered modules with missing responses identified as such.

A trial-specific DAWBA report will be prepared for each participant, based on a standard, study-specific template (online supplemental appendix 4). The algorithm-derived diagnostic predictions will be used to highlight the likelihood of a CYP meeting International Classification of Diseases (ICD-10) criteria for the disorders assessed; the report is based entirely on the algorithm-derived predictions and is not clinically rated. The report will be sent to participants (via post or email) and CAMHS clinicians (via upload to the clinical record), as an adjunct to usual clinical practice.

10.1136/bmjopen-2021-053043.supp4Supplementary data

#### Control

CYP randomised to the control arm will receive usual care (ie, referral review as usual). Based on standard information provided with the referral a clinical decision is made about whether the referral is accepted and, if so, a clinician conducts the initial CAMHS assessment as per usual practice in the service.

### Sample size

A target sample size of 1210 participants will be recruited and randomised, with equal allocation to intervention or control.

Assuming 45% of control participants have a confirmed diagnosis within 12 months (based on unpublished data obtained from the trial sites), detection of an absolute increase of 10% with 90% power and 5% two-sided alpha, requires 544 participants per arm for analysis. Allowing for up to 10% non-collection of the primary outcome, we will randomise 1210 participants.

### Measures and outcomes

#### Primary outcome

The primary outcome is a clinician-made diagnosis decision about the presence of an emotional disorder within 12 months of randomisation, that is, diagnosis of an emotional disorder will be coded as ‘yes’; absence or uncertainty (for example, reflecting ongoing assessment or investigation) will be coded as ‘no’. Eligible diagnoses are those that reflect ‘emotional’ or ‘internalising’ disorders in ICD/DSM (online supplemental appendix 5). The diagnosis must be documented in the clinical record within 12 months of randomisation by a mental health services clinician in an NHS-delivered or NHS-commissioned service.

10.1136/bmjopen-2021-053043.supp5Supplementary data

Diagnoses will be collected from clinical records using a standard proforma. Alternative possible diagnoses identified from the clinical notes will be recorded verbatim on the data capture form and will be subject to adjudication by members of the TMG (online supplemental appendix 6).

10.1136/bmjopen-2021-053043.supp6Supplementary data

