Any treatment/interventions given	Collected from records	All treatments/interventions offered by CAMHS for any reason within 12 months of randomisation, whether or not there is a documented diagnosis will be included.
Time from randomisation to the decision to offer treatment for a diagnosed emotional disorder	Collected from records	Date of decision will be the first date that the decision to offer treatment for a diagnosed emotional disorder is documented in the clinical notes, collected within 12 months of randomisation.
Time from randomisation to start of first treatment for a diagnosed emotional disorder	Collected from records	Date of treatment will be the first date that any treatment offered for a diagnosed emotional disorder is started. Treatment and diagnosed emotional disorder as defined, collected within 12 months of randomisation.
Time from randomisation to the decision to offer any treatment	Collected from records	Date of decision will be the first date that the decision to offer any treatment is documented in the clinical notes, collected within 12 months of randomisation.
Time from randomisation to start of any treatment	Collected from records	Date of treatment will be the first date that any treatment offered is started. Treatment as defined, collected within 12 months of randomisation.
Participant-reported diagnoses received in the 12 months post-randomisation	Participant self-report	Participants will be asked to report whether or not they received a diagnosis of the child/young person’s difficulties from CAMHS in the 12 months post-randomisation and if so, what diagnosis was given and by whom.
Depression symptoms in the CYP	Mood and Feelings Questionnaire (MFQ)	MFQ^30^ is a valid and reliable measure of depression in CYP.^31 32^ 33 items are answered on a 3-point scale (‘not true’=0, ‘somewhat true’=1 point, ‘true’=2 points). Scores range from 0 to 66 with higher scores indicating more severe depressive symptoms. A score of 27 or higher may be indicative of depression. MFQ collected at baseline, 6 and 12 months post-randomisation.

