#### Statistical analysis

The primary approach to between-group comparative analyses will be by modified intention to treat (ITT) (ie, including all participants who have been randomised and without imputation of missing outcome data).

The primary comparative analysis will employ a generalised linear mixed model to compare the proportions in each group with a clinician-made diagnosis decision within 12 months of randomisation, adjusted for minimisation variables. The comparison will be presented as both an absolute (risk difference) and relative (risk ratio) effect, along with 95% CIs.

Secondary outcomes will be analysed using appropriate mixed effect regression models dependent on data type and will adjust for factors used in the minimisation and baseline value of the outcome where measured. For outcomes measured at multiple time points, these will be analysed using a mixed model with a treatment by time interaction to obtain estimates of treatment effect at each follow-up time.

Appropriate interaction terms will be included in the primary regression analyses in order to conduct subgroup analyses according to sex and age of the CYP.

Statistical analysis will be conducted using Stata V.17.0 (or later).

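### The primary outcome counts recorded emotional-disorder diagnoses without an accuracy check, and the stated primary model and subgroups leave out the MFQ and RCADS scores collected before randomisation

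*Protocol article*

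**What the plan says.** All references are to the protocol article.

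- **Outcome (Primary outcome):** a "clinician-made diagnosis decision about the presence of an emotional disorder" within 12 months of randomisation.
- **Outcome coding (Primary outcome):** "diagnosis of an emotional disorder will be coded as ‘yes’; absence or uncertainty (for example, reflecting ongoing assessment or investigation) will be coded as ‘no".
- **Who makes the diagnosis (Primary outcome):** "The diagnosis must be documented in the clinical record within 12 months of randomisation by a mental health services clinician".
- **Adjudication (Primary outcome):** "Alternative possible diagnoses identified from the clinical notes will be recorded verbatim on the data capture form and will be subject to adjudication". Under Randomisation and concealment, the adjudicators are blind to arm and participant ID. Their rules are in an appendix that is not shown.
- **Intervention (Development and Well-Being Assessment):** "the report is based entirely on the algorithm-derived predictions and is not clinically rated". The report goes to families and is uploaded to the clinical record. The trial provides it in the intervention arm only.
- **Primary analysis (Statistical analysis):** the arms are compared on the outcome "within 12 months of randomisation, adjusted for minimisation variables". Those variables are site, age band and sex. Subgroup analyses of the primary outcome are by sex and age. Adjustment for a baseline value is stated only for secondary outcomes.
- **Baseline scores (Table 2):** MFQ and RCADS are collected at baseline, 6 and 12 months. Of the MFQ the table says: "A score of 27 or higher may be indicative of depression".
- **Timing (Randomisation and concealment):** randomisation is generated "following submission, and automated verification, of baseline data by the primary participant".

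**The concern.** The outcome moves in one direction. A clinician who reaches an eligible emotional diagnosis scores yes; one who correctly rules it out scores no, the same as one who is still undecided. Only the secondary outcome on confirmed diagnosis decisions credits a rule-out. The intervention hands unblinded clinicians a list of probable diagnoses, and referrals qualify whatever the severity of the emotional difficulties, so some participants may fall below the threshold for a disorder. A difference between arms could therefore mix better identification of children with a disorder and more diagnosing of children without one. The article's rationale rests on the first.

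The planned primary comparison and its two subgroup analyses give no information on that mix. Scores that bear on it at group level are already collected, before allocation for the primary participant, but have no stated role in the analysis of the primary outcome. At stake are how a positive result may be described, which matters because the aims include practice guidelines, and a small amount of precision.

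**Working it through.** **Inputs from the article (Sample size):** control rate 45%; increase of 10 points, so 55%; power 90%; two-sided alpha 5%; 544 per arm analysed; 10% non-collection; 1210 randomised.

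**1. The plan's own figure.** Without continuity correction, n = [1.960·√(2·0.5·0.5) + 1.282·√(0.45·0.55 + 0.55·0.45)]² / 0.10² = 523.3, so 524 per arm. With continuity correction, n = (523.3/4)·[1 + √(1 + 4/(523.3·0.10))]² = 543.1, so 544. Then 544/0.9 = 604.4, so 605 per arm and 1210 in total. The sample size reproduces exactly and is not in question.

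**2. What that calculation sees.** The standard error of the risk difference is √[(0.45·0.55 + 0.55·0.45)/544] = 0.0302, and power at 544 per arm is 91.1% (no continuity correction). Ten points are about 54 of 544 participants. An observed excess of about 6 points (about 33 participants) already reaches two-sided p < 0.05. These figures are the same whether or not the extra diagnoses are correct.

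**3. Could wrong diagnoses alone move the outcome?** The article gives no false-positive rate for the tool and no rate at which clinicians adopt its output, so this step is assumption only. Suppose there is no true gain and the control rate is 45%. Then extra yes = (share without a disorder) × (false-positive rate) × (share adopted).

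| Without disorder | False positive | Adopted | Extra yes | Chance of significance |
|---|---|---|---|---|
| 30% | 20% | 50% | 3 points | 17% |
| 40% | 30% | 50% | 6 points | 51% |
| 50% | 20% | 100% | 10 points | 91% |

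The range is too wide to support any claim about size. It shows only that the endpoint cannot exclude the mechanism.

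**4. Baseline scores as covariates.** If the scores explain a share R² of outcome variance (an assumption), the effective number per arm is about 544/(1 − R²).

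| R² | Effective n per arm | SE of risk difference | Power |
|---|---|---|---|
| 0 | 544 | 0.0302 | 91.1% |
| 0.03 | 561 | 0.0297 | 91.9% |
| 0.05 | 573 | 0.0294 | 92.4% |
| 0.10 | 604 | 0.0286 | 93.6% |

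**5. Treatment by baseline symptoms.** Assume a half split on severity (272 per arm in each half) and 45% in controls in both halves. With a 10-point gain in each half, the SE of the difference between the two risk differences is √[4·(0.45·0.55)/272] = 0.0603, and the 95% interval is ±1.96·0.0603, or ±11.8 points. Power depends on the pattern:

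- 20 points in one half and 0 in the other: SE 0.0597, power about 92%.
- 15 and 5 points: SE 0.0602, power about 38%.

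The analysis would show an extreme pattern and usually miss a moderate one.

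**The case against.** **The endpoint fits the objective.** The first listed objective is the effect on diagnosis and treatment, and the outcome measures diagnosis. Treatment offered, symptoms and impairment at 6 and 12 months, confirmed diagnosis decisions and QALYs all test whether extra diagnoses help. This stands, and it is why the endpoint should stay. None of those outcomes shows which children received the extra diagnoses.

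**The analysis plan may cover it.** A full statistical analysis plan is promised before database lock and is not shown. It could add such an analysis. But the article does not leave this open: it states the primary covariates and the subgroups, and the baseline scores are in neither.

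**Copied labels.** A reader might infer that a wrong algorithm prediction counts as success simply by being in the record. The article does not support that: a mental health clinician must make and document an eligible diagnosis, uncertainty scores no, and alternative possible diagnoses go to blinded adjudication. What remains is narrower. A clinician who adopts a wrong prediction scores yes, and nothing in the article describes adjudication as testing whether a documented diagnosis is true.

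**Baseline scores as arbiter.** A reader might also infer that MFQ and RCADS could separate true from false diagnoses. They cannot. The MFQ threshold is only indicative. The people who complete these scales also complete the DAWBA, so someone who over-reports could produce both a high baseline score and a false prediction. The tool covers specific phobia and post-traumatic stress disorder, which neither scale is described as measuring, so a correct diagnosis could fall in a child with low scores. This objection stands in full and rules out making any claim of improved detection depend on the interaction.

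**The precision gain is small.** True: 1 to 3 points of power under the assumed R², in a trial already powered at about 91%. Adjusting for the minimisation variables alone is valid, and covariates do nothing about diagnostic accuracy.

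**Conclusion.** The point holds in limited form. The primary outcome measures how many emotional-disorder diagnoses are recorded, without an accuracy check, and the stated primary analysis makes no use of symptom scores collected before allocation. Two modest things are lost: precision worth about 1 to 3 points of power, if baseline scores explain 3-10% of outcome variance, and a group-level view of where extra diagnoses fall, with a 95% interval of about ±12 points if the sample splits in half on severity.

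The documents do not support a conclusion that the trial would mainly reward false positives; any inflation is assumption only. Nor do they show that the endpoint or sample size is wrong. A significant primary result supports the statement that more emotional-disorder diagnoses were recorded. Calling it improved detection goes beyond what this outcome measures.

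**What to change.** Keep the endpoint and the sample size, and make three changes of wording:

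1. **Primary model.** Add the primary participant's baseline MFQ and RCADS total anxiety scores as covariates beside the minimisation variables. Use the primary participant's report because only that report is required before allocation.
2. **Exploratory analysis.** Prespecify a treatment-by-baseline-symptom analysis of the primary outcome with the scores kept continuous, and show diagnosis rates by arm across levels of severity. Label it exploratory and attach no decision rule to it.
3. **Interpretation.** State that a positive primary result will be described as more emotional-disorder diagnoses recorded.

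The cost is plan wording and one extra model on data already collected, with no added participant burden. The downsides should be stated with the analysis: the interaction is imprecise; the informant changes with age band (parent or carer under 16, young person at 16-17); the scales do not cover every eligible disorder; and continuous covariates may call for some convergence work in a binomial mixed model that has to yield both a risk difference and a risk ratio.

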#### Secondary outcomes

Secondary outcomes are detailed in table 2.

**Table 2 T2:** Secondary outcome definitions

Outcome	Measurement	Definition
Acceptance of index referral	Collected from records	Whether the index referral (ie, the referral made to CAMHS at the point of recruitment to the STADIA trial) was accepted or declined. Acceptance is defined as being offered an appointment within CAMHS, whether or not the initial appointment was attended or subsequent appointments were offered/attended. Collected within 12 months of randomisation.
Acceptance of any referral within 12 months of randomisation	Collected from records	Whether the index referral or any subsequent referral to CAMHS (if made) was accepted or not. Acceptance as defined above for index referral. Collected within 12 months of randomisation.
Discharge from CAMHS within 12 months	Collected from records	Whether the child/young person was discharged from CAMHS (following acceptance of the index referral) during the 12 months post-randomisation.
Re-referral to CAMHS within 12 months	Collected from records	Whether the child/young person was re-referred to CAMHS (for those whose index referral was turned down by CAMHS or those whose index referral was accepted but were subsequently discharged) during the 12 months post-randomisation.
Confirmed diagnosis decision	Collected from records	Diagnosis of an emotional disorder or confirmed absence of an emotional disorder coded as ‘yes’ versus uncertainty about the presence of an emotional disorder coded as ‘no’. Diagnosis as defined for primary outcome, collected within 12 months of randomisation.
Time from randomisation to diagnosis of emotional disorder	Collected from records	Date of diagnosis will be the first documented eligible diagnosis.Diagnosis as defined for primary outcome, collected within 12 months of randomisation.
Diagnoses made over the 12 month period from randomisation	Collected from records	The diagnosis must be documented in the clinical record within 12 months of randomisation by a mental health services clinician in an NHS-delivered or NHS-commissioned service. All diagnoses made within 12 months will be included. Measured using a standard proforma (pre-specified diagnoses).
Treatment offered for diagnosed emotional disorder	Collected from records	Whether treatment was offered for a diagnosed emotional disorder, as defined for primary outcome, collected within 12 months of randomisation.
Any treatment/interventions given	Collected from records	All treatments/interventions offered by CAMHS for any reason within 12 months of randomisation, whether or not there is a documented diagnosis will be included.
Time from randomisation to the decision to offer treatment for a diagnosed emotional disorder	Collected from records	Date of decision will be the first date that the decision to offer treatment for a diagnosed emotional disorder is documented in the clinical notes, collected within 12 months of randomisation.
Time from randomisation to start of first treatment for a diagnosed emotional disorder	Collected from records	Date of treatment will be the first date that any treatment offered for a diagnosed emotional disorder is started. Treatment and diagnosed emotional disorder as defined, collected within 12 months of randomisation.
Time from randomisation to the decision to offer any treatment	Collected from records	Date of decision will be the first date that the decision to offer any treatment is documented in the clinical notes, collected within 12 months of randomisation.
Time from randomisation to start of any treatment	Collected from records	Date of treatment will be the first date that any treatment offered is started. Treatment as defined, collected within 12 months of randomisation.
Participant-reported diagnoses received in the 12 months post-randomisation	Participant self-report	Participants will be asked to report whether or not they received a diagnosis of the child/young person’s difficulties from CAMHS in the 12 months post-randomisation and if so, what diagnosis was given and by whom.
Depression symptoms in the CYP	Mood and Feelings Questionnaire (MFQ)	MFQ^30^ is a valid and reliable measure of depression in CYP.^31 32^ 33 items are answered on a 3-point scale (‘not true’=0, ‘somewhat true’=1 point, ‘true’=2 points). Scores range from 0 to 66 with higher scores indicating more severe depressive symptoms. A score of 27 or higher may be indicative of depression. MFQ collected at baseline, 6 and 12 months post-randomisation.
Anxiety symptoms in the CYP	Revised CYP’s Anxiety Depression Scale (RCADS)	RCADS^33^ is a 47-item questionnaire that measures the reported frequency of various symptoms of anxiety and low mood. Each item is rated on a 4-point scale (never=0, sometimes=1, often=2, always=3). An overall anxiety and low mood score is generated, with separate sub-scale scores for separation anxiety, social phobia, generalised anxiety, panic, obsessive–compulsive disorder and major depression. RCADS demonstrates good psychometric properties.^34^ Total anxiety and depression scores range from 0 to 141. We will record scores for each of the six sub-scales. For analysis metric, we will use the total anxiety score. RCADS collected at baseline, 6 and 12 months post-randomisation.
Comorbid oppositional defiant/conduct disorder symptoms in the CYP	Strengths and Difficulties Questionnaire (SDQ)	SDQ^35^: A 25-item emotional and behavioural screening questionnaire for CYP. Each item is rated on a 3-point scale (not true, somewhat true, certainly true). Values of 0, 1 or 2 are assigned to each response. SDQ comprises five subscales and an impact supplement. The impact supplement asks effect of difficulties on homelife, friendships, education and leisure activities. SDQ has demonstrated reasonable psychometric properties.^36–39^ Scores on the ‘conduct problems’ subscale will be used in the analysis of this outcome. Subscale scores range from 0 to 10. SDQ collected at baseline, 6 and 12 months post-randomisation.
Functional Impairment in the CYP	SDQ	Impact supplement scores will be used to determine functional impairment. Impact scores range from 0 to 10. Collected at baseline, 6 and 12 months postrandomisation.
Self-harm thoughts in the CYP	CYP self-report self-harm measure	CYP will be asked to report the frequency of thoughts of self-harm. Frequency of thoughts of self-harm are rated over the last 6 months in the following categories and scored accordingly: Not at all (0) Once or twice Three or more times Collected at baseline, 6 months and 12 months post-randomisation.
Self-harm behaviours in the CYP	CYP self-report self-harm measure	CYP will be asked to report frequency of instances of self-harm behaviour. Frequency of self-harm behaviour are rated over the last 6 months in the following categories and scored accordingly: Not at all (0) Once Two or more times Collected at baseline, 6 months and 12 months post-randomisation.
Depression symptoms in the parent/carer	Patient Health Questionnaire (PHQ-9)	PHQ-9:^40^ PHQ-9 is frequently used as a screening tool for depression in general populations. Each of the nine DSM-IV depression criteria are scored as ‘0’ (not at all) to ‘3’ (nearly every day) depending on the frequency with which they were experienced over the last 2 weeks. Total scores range from 0 to 27 with higher scores indicating increased severity of depression, collected at baseline, 6 and 12 months post-randomisation.
Anxiety symptoms in the parent/carer	Generalised Anxiety Disorder Assessment (GAD-7)	GAD-7:^41^ GAD-7 is a measure of the severity of anxiety in general populations. 7 items are rated according to the frequency with which they have been experienced over the past 2 weeks (0 = ‘not at all’, 1 = ‘several days’, 2 = ‘more than half the days’ and 3 = ‘nearly every day’). Total scores range from 0 to 21 with higher scores indicating more severe anxiety. Collected at baseline, 6 and 12 months post-randomisation.
Time off education, employment or training because of emotional difficulties for the CYP	Resource use questionnaire	Days missed from education, employment or training (as applicable) for the CYP due to emotional difficulties. Collected at baseline, 6 and 12 months post-randomisation.
Health economic outcome measures		
Health-related quality of life in the CYP	Child Health Utility 9D (CHU9D) and EuroQol Quality of Life Questionnaire 5 Domains for Young People (EQ-5D-Y)	CHU9D^42^ consists of nine individual items with five levels of response per question (scored 1–5), that assess the CYP functioning ‘today’. The following domains are included; worry, sadness, pain, tiredness, annoyance, school, sleep, daily routine and activities. EuroQol-5D youth descriptive system^43^ comprises five domains; mobility, looking after myself, doing usual activities, having pain or discomfort and feeling worried, sad or unhappy, values of 1, 2 or 3 are assigned to each response. The EuroQol Visual Analogue Scale (EQ-VAS) asks recipients to self-assess their health state ‘today’ from 0 (worst imaginable health) to 100 (best imaginable health), representing individual preferences. These measures will be self-reported by CYP aged 11+, with proxy versions also completed by the parent/carer for CYP <16. Both collected at baseline, 6 and 12 months post-randomisation.
Health-related quality of life in the parent/carer	EuroQol Quality of Life Questionnaire 5 Domains, 5 Levels (EQ-5D-5L)	The EuroQol 5-dimension multi attribute utility instrument^44^ comprises five domains; mobility, self-care, usual activities, pain/discomfort and anxiety/depression. Each domain is scored between 1 and 5. This descriptive profile, in combination with a valuation set, produces a single index for health status representing societal preferences. The index score ranges from −0.59 to 1, with 0 representing death, 1 of-perfect health and <0 of health states worse than death. The EQ-VAS is again included within the EQ-5D instrument Collected at baseline, 6 and 12 months post-randomisation.

CAMHS, Child and Adolescent Mental Health Services; CYP, children and young people; NHS, National Health Service; STADIA, STAndardised DIagnostic Assessment for children and adolescents with emotional difficulties.

